#### Economical evaluation

Costs will be linearly interpolated to estimate total costs covered by the time period between consecutive assessments. Unit prices will be determined according to Dutch guidelines, expressed in 2016 Euros and will be indexed if necessary using consumer price indices. Otherwise, integral cost-prices will be obtained from the Maastricht University Medical Center, or cost-price calculations will be performed.

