### (Clinical) effectiveness

To assess the (clinical) effectiveness of both procedures, patients are asked to fill out web based questionnaires concerning Patient Related Outcome Measurements (PROMS) at five fixed time-points, namely preoperatively and 3, 6, 12 and 24 months postoperatively.

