#### Economic evaluation

The economic evaluation will assess cost-effectiveness (CEA) and cost-utility (CUA) from a societal and health care perspective. Costs will be related to change in disability measured with ODI and change in cost-effectiveness analysis and to changes in quality-adjusted life years (QALYs) with EQ-5D-5L in the cost-utility analysis. The analysis will be performed with a time horizon of two years.

Data are collected in web based CRFs (case report forms) and by means of questionnaires. Included costs consist of: 1. health care costs, 2. patient and family costs and 3. other costs. Healthcare costs are for example costs of surgical intervention (either TLIF or PLIF), hospital care (including costs for treating complications), medication, outpatient visits and resource use outside the hospital such as general practitioner visits and physical therapist visits. Among patient and family costs are travel costs, informal care and home care. Other costs are costs such as productivity losses due to absence from work. Information on these costs will be collected with a questionnaire designed for consumption of healthcare in the Dutch system (Medical Consumption Questionnaire - iMCQ) and a questionnaire designed for productivity costs in the Dutch system (Productivity Costs Questionnaire iPCQ). Both questionnaires have a recall period of 3 months and will be administered repeatedly at five fixed time points.

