#### Patient outcome analysis

The primary clinical outcome is the change in disability measured with ODI, over the course of a two year follow-up period, to which total societal costs will be related in the CEA. For the CUA, utilities are assessed using the EQ-5D-5L [14]. These utilities will be converted following the area under the curve method into QALYs using the United Kingdom social tariffs. Changes in QALYs over the course of the two-year follow-up period will be related to total societal costs in the CUA [20].

Costs and effects will be discounted according to Dutch pharmaco-economic guidelines. Standard sensitivity analyses and bootstrap analysis will be performed to investigate the uncertainty surrounding the cost-effectiveness ratios [21]. Based on the bootstrap results, cost-effectiveness acceptability curves will be constructed, showing threshold values for a wide range of cost-effectiveness, the probability that TLIF is more cost-effective.

In addition to the CEA and CUA, a model-based simulation approach will be used to assess generalizability of the findings.

The Budget Impact Analyses (BIA), alongside the CEA, will be performed to address the financial consequences of implementing the most cost-effective treatment as intervention of choice in patients with lumbar spondylolisthesis. The BIA is based on the results of the clinical trial and will be conducted according to the ISPOR guidelines and Dutch guideline for executing economic evaluations in health care [20, 22] from various perspectives: (i) wider societal perspective, i.e. including productivity losses; (ii) a narrower perspective of the public purse (in Dutch: Budgettair Kader Zorg (BKZ)); (iii) the perspective of the health care insurer. All scenarios will be compared with a reference scenario which consists of the current standard of performing both TLIF and PLIF. The BIA will be estimated for various implementation levels (10, 25, 50 and 100 % of the intended target group). Furthermore, scenarios will be modelled in which the timeline of implementing the most cost-effective treatment as intervention of choice in 100 % of the hospitals is varied between direct implementation to implementation in five years.

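### Linear interpolation is applied to all costs although the 3-month-recall forms observe only 12 of 24 months, so any one-off cost taken from those forms is multiplied or lost

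*Protocol article*

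**What the plan says.** Four statements in the protocol article combine here.

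- **Recall** (Economic evaluation): "Both questionnaires have a recall period of 3 months and will be administered repeatedly at five fixed time points".
- **Timing** ((Clinical) effectiveness): questionnaires are completed at five points, "namely preoperatively and 3, 6, 12 and 24 months postoperatively".
- **Horizon** (Economic evaluation): "The analysis will be performed with a time horizon of two years". Under Patient outcome analysis, total societal cost over this period is set against ODI change in the cost-effectiveness analysis and against QALYs in the cost-utility analysis: "Changes in QALYs over the course of the two-year follow-up period will be related to total societal costs in the CUA".
- **Filling rule** (Economical evaluation): "Costs will be linearly interpolated to estimate total costs covered by the time period between consecutive assessments".

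The costs in scope include "hospital care (including costs for treating complications"). On their source, the same section says: "Information on these costs will be collected with a questionnaire designed for consumption of healthcare in the Dutch system", and adds a second questionnaire for productivity. It also opens with "Data are collected in web based CRFs (case report forms) and by means of questionnaires", but does not say which cost items, if any, come from the CRFs.

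**The concern.** Interpolation is reasonable for costs that run on at a slowly changing rate, such as physiotherapy or medication. It does not suit an admission or the treatment of a complication, which happens once. If such an event falls in an observed quarter next to a gap, interpolation spreads copies of it into the gap. If it falls inside a gap, it is never seen.

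The filling rule makes no distinction between these kinds of cost. At stake is the two-year total cost, which feeds the cost-effectiveness and cost-utility analyses and, through the trial results, the budget impact analysis. With 144 patients, a few late admissions counted three times or not at all could move the cost difference between the arms. Complications are to be analysed over the whole 24 months, so an event in months 12-21 could count clinically and yet be costed at zero.

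**Working it through.** The protocol gives no figure for cost coverage, so there is none to reproduce. The inputs are the recall period (3 months), the post-operative assessments (3, 6, 12 and 24 months) and the horizon (24 months), all from the sections cited above.

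**Coverage.** A form at month t covers months t-3 to t. The four post-operative forms cover 0-3, 3-6, 9-12 and 21-24, so 4 × 3 = 12 months, or 12/24 = 50%. The gaps are 6-9 (3 months) and 12-21 (9 months). The pre-operative form covers no post-operative time. Contiguous coverage by 3-month recall would need 24/3 = 8 post-operative forms against the 4 planned.

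**Weights, reading A: interpolate quarterly costs between observed quarters.** Number the quarters 1 to 8; those observed are 1, 2, 4 and 8.

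- Quarter 3 is the mean of quarters 2 and 4, giving 0.5 to each.
- Quarters 5, 6 and 7 run linearly from quarter 4 to quarter 8. Quarter 4 receives 0.75 + 0.5 + 0.25 = 1.5, and quarter 8 receives 0.25 + 0.5 + 0.75 = 1.5.
- Totals: quarter 1 = 1; quarter 2 = 1 + 0.5 = 1.5; quarter 4 = 1 + 0.5 + 1.5 = 3; quarter 8 = 1 + 1.5 = 2.5. The sum is 8.

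**Weights, reading B: trapezoid on the cost rate at 0, 3, 6, 12 and 24 months.** Each form's weight, in quarters, is half the length of its adjoining intervals divided by 3.

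- Month 0: 3/2/3 = 0.5
- Month 3: (3+3)/2/3 = 1
- Month 6: (3+6)/2/3 = 1.5
- Month 12: (6+12)/2/3 = 3
- Month 24: 12/2/3 = 2

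The sum is again 8, but 0.5 of it falls on the pre-operative quarter.

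| One-off cost C falls in months | Counted, A | Counted, B |
|---|---|---|
| 0-3 | 1.0 C | 1.0 C |
| 3-6 | 1.5 C | 1.5 C |
| 6-9 | 0 | 0 |
| 9-12 | 3.0 C | 3.0 C |
| 12-21 | 0 | 0 |
| 21-24 | 2.5 C | 2.0 C |

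Under either reading, an admission in month 10 counts as 3C and the same admission in month 15 counts as 0.

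**Mean and variance, assuming rare events spread evenly over 24 months.**

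- Mean weight: A, 8/8 = 1.0; B, (1 + 1.5 + 3 + 2)/8 = 7.5/8 = 0.94.
- Share of events counted as zero: 4 of 8 quarters, 50%.
- For rare events, the variance of this cost component scales with the mean squared weight, which would be 1 under full observation. A: (1 + 2.25 + 9 + 6.25)/8 = 18.5/8 = 2.3. B: (1 + 2.25 + 9 + 4)/8 = 16.25/8 = 2.0.

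**Late events only, assuming an even spread over months 6-24 (six quarters).** Four of six quarters, or two thirds, count as zero. The mean weight is 5.5/6 = 0.92 (A) or 5/6 = 0.83 (B).

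**The case against.** The strongest reply is that one-off hospital costs may never pass through the questionnaires. The article names web-based CRFs as a data source, registers complications including hardware failure, analyses complications up to 24 months, records length of hospital stay, and foresees hospital cost prices. A recall form is also an implausible sole source for the cost of the index operation. This stands in part. A reader might infer that complication costs will in fact be miscounted in this trial, and the document does not establish that. But the filling rule is stated, not left open; it exempts nothing, and no cost item is assigned to the CRF.

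Three other stronger readings are tempting and are not supported.

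- **That the comparison of arms is biased.** Evenly spread events leave the mean about right, and nothing in the article shows that late-event timing differs between TLIF and PLIF. The cost drivers that the article names include surgical morbidity, hospital stay and operating time; these fall mainly in months 0-3, where the weight is 1.
- **That the bootstrap intervals are too narrow because filled values pass as observed.** The filled values are fixed linear functions of each patient's observed quarters, so resampling patients carries the inflated variance. What it cannot do is recover events nobody asked about, or test the interpolation assumption.
- **That pre-operative costs enter the post-operative total.** This follows only from reading B, which is strained because the 3-month form already covers months 0-3. The wording does not exclude it, so it merits a clarifying sentence and no more.

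It is also fair that the variance ratio applies to the one-off component alone. Its effect on total cost, which includes the index operation and recurrent items, cannot be derived from the document.

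**Conclusion.** The point holds as a poorly fixed rule for one class of costs. That the questionnaires observe 12 of 24 months is exact. For any one-off cost taken from them, the stated rule gives a weight of 1.5 in months 3-6, 3 in months 9-12, 2 to 2.5 in months 21-24, and zero in months 6-9 and 12-21; months 0-3 are unaffected.

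If such events are rare and evenly spread, the mean is about unbiased and the variance of that component is about 2.0 to 2.3 times its true value. Bias arises only if late-event timing differs by arm. The conclusion is conditional on one-off costs coming from the questionnaires: those costed from continuous, dated records would escape the effect. Productivity loss, informal care and other questionnaire-only items would still rest on interpolation in both gaps, which is acceptable for recurrent costs if it is tested. ODI and QALY results are untouched. This should be corrected before the economic analysis.

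**What to change.** In the Economical evaluation section:

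1. Restrict linear interpolation to recurrent questionnaire items (for example GP visits, physiotherapy, medication, informal care and work absence) and to months 6-9 and 12-21.
2. Cost admissions and treatment of complications at their actual dates, from the CRF and the complication registration already kept over 24 months, and say which cost items come from that source.
3. State that the pre-operative form does not enter post-operative totals.
4. Name a sensitivity analysis of the interpolation assumption among the planned sensitivity analyses.

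Visits, treatment and sample size do not change. The cost is some data-management time to extract and date hospital events. Events treated outside the trial hospitals may be missed, and that should be reported as a limitation.

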#### Patient outcome analysis

The primary clinical outcome is the change in disability measured with ODI, over the course of a two year follow-up period, to which total societal costs will be related in the CEA. For the CUA, utilities are assessed using the EQ-5D-5L [14]. These utilities will be converted following the area under the curve method into QALYs using the United Kingdom social tariffs. Changes in QALYs over the course of the two-year follow-up period will be related to total societal costs in the CUA [20].

Costs and effects will be discounted according to Dutch pharmaco-economic guidelines. Standard sensitivity analyses and bootstrap analysis will be performed to investigate the uncertainty surrounding the cost-effectiveness ratios [21]. Based on the bootstrap results, cost-effectiveness acceptability curves will be constructed, showing threshold values for a wide range of cost-effectiveness, the probability that TLIF is more cost-effective.

In addition to the CEA and CUA, a model-based simulation approach will be used to assess generalizability of the findings.

The Budget Impact Analyses (BIA), alongside the CEA, will be performed to address the financial consequences of implementing the most cost-effective treatment as intervention of choice in patients with lumbar spondylolisthesis. The BIA is based on the results of the clinical trial and will be conducted according to the ISPOR guidelines and Dutch guideline for executing economic evaluations in health care [20, 22] from various perspectives: (i) wider societal perspective, i.e. including productivity losses; (ii) a narrower perspective of the public purse (in Dutch: Budgettair Kader Zorg (BKZ)); (iii) the perspective of the health care insurer. All scenarios will be compared with a reference scenario which consists of the current standard of performing both TLIF and PLIF. The BIA will be estimated for various implementation levels (10, 25, 50 and 100 % of the intended target group). Furthermore, scenarios will be modelled in which the timeline of implementing the most cost-effective treatment as intervention of choice in 100 % of the hospitals is varied between direct implementation to implementation in five years.

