### Setting and recruitment

This is a cooperating project involving six Dutch hospitals (Maastricht University Medical Center - Maastricht, Zuyderland Medical Center - Heerlen, University Medical Center Groningen - Groningen, Radboud university medical center - Nijmegen, Canisius Wilhelmina Hospital - Nijmegen and Isala - Zwolle). These hospitals have been chosen because of their high volume of instrumented spine surgery and their familiarity with TLIF and PLIF. Patients referred to the outpatient clinic with an indication for LIF surgery are eligible to participate in the study, and will be referred by colleagues to the researchers.

Researchers will inform the patient verbally and in writing. When the patient is willing to participate (patients are allowed to use a cooling off period of one week) an informed consent form will be signed by the patient and the researcher, and patients will be allocated randomly to either the TLIF or PLIF group.

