## Discussion

This study will determine the clinical effectiveness and cost-effectiveness of TLIF compared to PLIF for patients with leg pain caused by single level lumbar spondylolisthesis. The demand for spinal fusion surgery has risen steeply over the last ten years and is expected to increase even further in the near future. In times of rising health care costs and resulting budget limitations, there is a need for solid, comparative, cost-effectiveness studies to be able to recommend the best choice, clinically as well as cost-effectively, of surgery for these patients. It is hypothesized that TLIF, compared to PLIF, is superior in reducing disability and thus has a better clinical outcome. Moreover, health care costs are suspected to be lower due to less surgical morbidity, shorter hospital stay and shorter surgical time. Productivity losses are assumed to be lower for TLIF as well, because less working days are lost.

Currently, the choice for technique is greatly based on surgeon’s experience and preference. The strength of this multicenter study is that because of randomization, the preference of the surgeon no longer determines which technique is used. Also this study is, to our knowledge, the first where cost-effectiveness of both procedures will be explored and compared.

One of the limitations of this study is the sample size. We do expect to be able to draw conclusions on the primary outcomes. However, for some of the secondary outcomes (for example complications) the sample size will be too small. We aim to see if results are comparable with those previously reported in literature.

Additionally, we will perform a process evaluation to assess the experiences and opinions of patients and professionals with TLIF.

In case our hypothesis is confirmed, this could lead to reduction of (healthcare and productivity losses) costs and better clinical outcome for spondylolisthesis patients eligible for instrumented spinal surgery. Recommendations considering the best choice will be very helpful for spine surgeons in the future and lead to adaptation of the current Dutch guidelines.

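### QALYs are valued with United Kingdom tariffs, without a stated reason, in an evaluation whose other country-specific inputs and intended use are Dutch

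*Protocol article*

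**What the plan says.** Under Patient outcome analysis, the protocol article states how EQ-5D-5L responses become QALYs: "These utilities will be converted following the area under the curve method into QALYs using the United Kingdom social tariffs". No other tariff appears anywhere in the article, so this one serves the main analysis by default. No reason is given for it.

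The other country-specific parts of the economic work are Dutch:

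- Setting and recruitment: "This is a cooperating project involving six Dutch hospitals". Inadequate command of Dutch is an exclusion criterion (Study population).
- Economic evaluation: resource use comes from "a questionnaire designed for consumption of healthcare in the Dutch system" and from a companion productivity questionnaire, also built for the Dutch system.
- Economical evaluation: "Unit prices will be determined according to Dutch guidelines, expressed in 2016 Euros".
- Patient outcome analysis: "Costs and effects will be discounted according to Dutch pharmaco-economic guidelines".
- Patient outcome analysis, budget impact: the work "will be conducted according to the ISPOR guidelines and Dutch guideline for executing economic evaluations in health care [20, 22", with the Dutch public health care budget and the health insurer among the perspectives.
- Discussion: the recommendations are expected to "lead to adaptation of the current Dutch guidelines".

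The Abstract and Primary outcomes list change in QALYs beside change in ODI as a primary outcome. Patient outcome analysis makes the QALY the effect measure of the cost-utility analysis.

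**The concern.** A QALY is survival time weighted by someone's preferences over health states, and the choice of tariff decides whose preferences those are. Here the QALY is weighted by United Kingdom preferences, discounted by Dutch rules, and set against costs priced by Dutch rules. The evaluation takes "The economic evaluation will assess cost-effectiveness (CEA) and cost-utility (CUA) from a societal and health care perspective" as its frame, and its result is meant for Dutch guidance. With that use in view, one would expect the population that bears the costs to value the health gained as well, or the plan to explain why not.

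The tariff enters the QALY primary outcome, the cost per QALY, its bootstrap distribution and the acceptability curve. It can reach the budget impact analysis indirectly, because that analysis models the adoption of whichever treatment proves most cost-effective. A Dutch reader who wanted Dutch values would have to ask for the QALYs to be scored again. The Abstract's Discussion allows that clinical outcome may be merely similar between the arms. A small QALY difference would make the ratio sensitive to its denominator.

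**Working it through.** **What the tariff does not touch.** The only sample size in the article is for the ODI. Inputs from Sample size calculation: difference 8, SD 16, power 0.8, type I error 0.05 (taken as two-sided).

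- Normal approximation: n per arm = 2 × (1.960 + 0.842)² × 16² / 8² = 2 × 7.85 × 4 = 62.8, so 63.
- With the t distribution: 63.8, so 64 per arm, as stated.
- With 10% loss: 64 / 0.9 = 71.1, so 72 per arm and 144 in total, as stated.

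No utility value enters, so the sample size stands whatever tariff is used. The cost totals and the ODI-based cost-effectiveness ratio also contain no utility value.

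**Which country's rules govern each part of the cost per QALY.**

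| Component | Rule named | Section |
|---|---|---|
| Resource use | Dutch-system questionnaires | Economic evaluation |
| Unit prices | Dutch guidelines, 2016 Euros | Economical evaluation |
| Discounting of costs and effects | Dutch guidelines | Patient outcome analysis |
| Health-state values | United Kingdom tariffs | Patient outcome analysis |

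The numerator is Dutch throughout. The denominator is valued by one country's tariff and discounted by the other's rules.

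**Size.** The article gives no tariff values, expected utilities or QALY difference, so the effect cannot be computed from it. A scaling model shows only how a change would carry through.

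*Assumption:* the between-arm QALY difference under Dutch values is k times the difference under United Kingdom values, with k > 0. Then

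cost per QALY (Dutch) = ΔC / (k × ΔQ) = (1/k) × cost per QALY (UK).

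| k (assumed) | Multiplier 1/k |
|---|---|
| 0.7 | 1.43 |
| 0.8 | 1.25 |
| 1.2 | 0.83 |
| 1.4 | 0.71 |

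For the acceptability curve, net benefit at threshold λ is λ × k × ΔQ − ΔC. If k applies to every bootstrap replicate, the Dutch-valued curve at λ equals the UK-valued curve at kλ, so the curve is stretched or compressed along the threshold axis.

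The values of k have no source in the document. Two tariffs also need not differ by a constant factor, because they may weight dimensions and levels differently. The table therefore shows a mechanism and does not bound the effect.

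**The case against.** The strongest reply is that nothing here contradicts anything else. The tariff is stated openly, and no passage promises Dutch values. The research question in Methods refers to a societal perspective without the word Dutch. The Dutch guidelines are tied by name to prices, discounting and budget impact, not to utility weights. Both arms are scored with the same tariff, so neither is favoured by design. If TLIF proves both better and cheaper, as the Discussion hypothesises, it stays dominant under any positive k, and a percentage change in a negative ratio would mean nothing. The QALYs can be re-scored at any time.

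Much of this stands, and it rules out several stronger readings:

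- *That the evaluation fails to answer the Dutch question.* The ODI-based analysis and the costs are untouched. The point is confined to the QALY outcome and what is built on it.
- *That the plan breaches the Dutch guideline.* The content of the cited guideline is not in the document, so a requirement for national values cannot be asserted.
- *That no Dutch valuation is planned at all.* Standard sensitivity analyses are announced without a list. One can say only that none with another tariff is named.
- *That every other element is Dutch.* The budget impact analysis also follows ISPOR guidelines.
- *That the ratio would shift by a known percentage.* The range for k is assumed.

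The availability of a Dutch value set for the EQ-5D-5L cannot be settled from the document either, and the fix has to allow for that.

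The reply does not remove the mismatch. The tariff is a choice the article makes affirmatively, not a detail left to a fuller document. It fits the stated use of the result poorly, and it is unexplained. Dominance is a hypothesis, and a plan should also serve the case in which it fails.

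**Conclusion.** The concern holds in a limited form. The protocol article values the QALY, a listed primary outcome and the effect measure of the cost-utility analysis, with United Kingdom tariffs and no stated reason. The other country-specific economic inputs and the intended guideline use are Dutch. The cost per QALY and the acceptability curve would therefore combine Dutch costs with United Kingdom preferences.

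The size is unknown from the document, and the multipliers of 1.25 and 0.83 rest wholly on the assumed k of 0.8 and 1.2. The conclusion needs neither those figures nor any external guideline requirement. It rests on the mismatch between the named tariff and the decision the analysis is meant to inform. The matter is worth correcting before results are known, but it does not threaten the trial's design, its data collection or its ODI analysis.

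**What to change.** In Patient outcome analysis, value the main-analysis QALYs with a Dutch EQ-5D value set applicable to the EQ-5D-5L, cite the set, and keep the United Kingdom tariff as a named sensitivity analysis. If no suitable Dutch set is available, state that as the reason for the tariff used and prespecify a sensitivity analysis with an alternative tariff.

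In the Clinical effectiveness part of the Analysis section, which names no tariff, state that EQ-5D-5L utilities are scored with the same value set, so that the clinical and economic reports agree. Settle this before outcome data are seen, so that the tariff cannot be chosen on the results.

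The change needs new scoring code and a second run of the cost-utility analysis. It needs no new patients, visits or questionnaires. The downside is slightly less comparability with studies that use United Kingdom values, and the sensitivity analysis preserves that comparison.
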